# Study Objectives

The study will test the extent to which an intervention designed to improve household perceptions of the efficacy of preventative care increases uptake of the service in Uttar Pradesh. It will use the DPT vaccine as a case study to examine this question. The specific objectives of the study are:

1. To examine whether providing accurate information regarding the effectiveness of DPT vaccine affects demand for and uptake of the service
2. To examine whether negative framing relative to positive framing enhances the effect of the information on service uptake
3. To examine whether the effect of information is greater amongst those who initially have lower perceptions of the efficacy of DPT vaccine

The study involves a randomised field experiment to test whether information given to households on the actual effectiveness of healthcare can shift perceptions thereby increasing demand and uptake. It would only be ethical to attempt to provide households with information on health interventions for which there is rigorous evidence on efficacy. The general principle will thus be tested using an information intervention specific to the DPT vaccine for which there is strong and widely accepted evidence on efficacy.

# Methods

## Study Design

A randomised field experiment will be used to provide information on the efficacy of the DPT vaccination to mothers with young children. Families will be individually randomised into three study arms. Mothers in the first treatment group will receive the information framed in positive terms. A second treatment group will provide essentially the same information on efficacy but framed in negative terms. The third arm acts as a control group with no information given to the mother. Randomisation will done using the digital equivalent of a three-sided coin. Enumerators will be blind to the assignment of the intervention.

Information will be given to mothers in the privacy of their own home. Nevertheless, randomisation at the individual household level gives rise to concerns of potential contamination. A household given one of the two information interventions may then interact and share information with the households in the control group. The extent to which information spills over to other neighbours and peers of treated households will be estimated in the standard way, as explained in Section 4.6, by exploiting random variation in the geographical density of households.

## Participants and Inclusion Criteria

The criteria for inclusion in the study include: 1) mother with a child aged 0-36 months living in the same household; 2) child has not received three doses of DPT vaccine; 3) mother gives consent to participate in the study; and 4) mother intends to remain in the study area for at least six months. The criteria for exclusion in the study include: 1) child of mother is not aged 0-36 months; 2) child of mother is not living in the same household; 3) child has received three doses of DPT vaccine; 4) mother does not give consent to participate in the study; and 5) mother due to emigrate from the study area in the next year.

## Outcomes

The primary outcome is the proportion of children with three doses of DPT vaccine as verified by the vaccination card or reported by the mother. This outcome will be measured at baseline and nine months. Secondary outcomes include: 1) the proportion of children fully vaccinated (against tuberculosis, diphtheria, pertussis, tetanus, polio and measles); 2) an index of the mother’s knowledge of tetanus symptoms, and 3) an index of the mother’s perception of the efficacy of tetanus vaccination. Characteristics of the study population will be obtained from the household survey at baseline and used to examine the balance of the treatment and control groups.

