| Notes: Sources are the Census 2011 and the Annual Health Survey 2012-13. The MMR estimates apply to groups of districts within the state due to sample size limitations. | | | | | | | |

A substantial proportion of children do not receive the vaccines recommended by the Government of India (Table 2). Just under two-thirds of children receive three doses of DPT in the state. Coverage of DPT3 in the study districts is either around the state average or above, with modest variation between districts. Coverage of measles largely mirrors that of DPT3. A higher proportion of children receive the BCG vaccine, the first of the routine immunisations given at birth. Only half of all children in the state are fully immunised against the six main vaccine preventable diseases implying that there are important barriers to uptake.

Table 2. Immunisation coverage for children aged 12-23 months

| Indicator | Uttar Pradesh | Kannauj | Kanpur Nagar | Kanpur Dehat | Auraiya | Etawah | Fatehpur |
| --- | --- | --- | --- | --- | --- | --- | --- |
| Children 12-23 months received 3 doses of DPT | 63.2 | 59.1 | 72.4 | 72.4 | 59.5 | 69.2 | 65.5 |
| Children 12-23 months received measles vaccine | 65.8 | 61.2 | 75.1 | 79.7 | 60.2 | 75.7 | 70.7 |
| Children 12-23 months with immunization card | 71.7 | 66.0 | 92.4 | 92.0 | 80.3 | 92.1 | 88.2 |
| Children 12-23 months received BCG vaccine | 86.3 | 90.5 | 89.4 | 92.6 | 84.9 | 91.3 | 91.1 |
| Children 12-23 months received 3 doses of polio | 64.1 | 59.1 | 73.2 | 70.8 | 60.2 | 72.7 | 65.5 |
| Children 12-23 months fully immunized | 52.7 | 46.4 | 59.2 | 61.9 | 46.2 | 58.0 | 51.5 |
| Notes: Source is the Annual Health Survey 2012-13. | | | | | | | |

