## Information Intervention

### Description of intervention

The study will test an intervention that provides mothers with information concerning the DPT vaccine. The information script will focus primarily on tetanus given that it has the greatest disease burden of the three diseases ([Million Death Study et al., 2010](#_ENREF_20)). Specifically, it will describe the symptoms of tetanus, possible health consequences, the individual benefit of the combination vaccine in terms of mortality and morbidity gains, wider community benefits associated with herd immunity, and where the family can get the child vaccinated at what cost and up until what age.

There will be two versions of the script. The first will frames the information on DPT vaccination as gains – eg. X% less likely to get tetanus, Y% more likely to live if the child is vaccinated and Z number of fewer tetanus deaths per year if every child was vaccinated in India. The second will frame information on DPT vaccination as losses – eg. X% more likely to get tetanus, Y% more likely to die if the child is not vaccinated and Z number of deaths per year because not every child is vaccinated in India. The information script will be delivered to the mother in the privacy of her own home. Visual aids will also be used to help provide the information in an accessible manner. There will a short question and answer session to ensure comprehension of the information.

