### Identification of participants

Potentially eligible participants were identified through two channels. First, a household survey conducted by the research team for a different purpose nine months prior to the study will be useful in identifying eligible women to participate. The household survey will use the sampling frame provided by the most recent census, conducted in 2011. The sampling is based on a two-stage design. The first stage involves the selection of 180 primary sampling units or clusters using systematic sampling proportional to size. The second stage involves a full household listing on entry to the cluster to create the sampling frame of eligible women (i.e. gave birth in previous two years). From this sampling frame 20 eligible women per cluster will be selected at random and invited for interview. Second, a list of mothers who have given birth in the past year provided by the community health worker (known as ASHAs) in each village will also identify eligible women to participate. Study researchers will visit the household of each potentially eligible mother, assess eligibility based on either vaccination cards or self-reports, and seek informed consent.

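### The primary outcome counts the unblinded mother's report equally with the vaccination card, so over-reporting in the information arms could pass for uptake

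*Protocol*

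**What the plan says.** The Outcomes section of the protocol defines the primary outcome as the proportion of children with "three doses of DPT vaccine as verified by the vaccination card or reported by the mother". It adds: "This outcome will be measured at baseline and nine months". The two sources are joined by a plain *or*. No sentence gives the card precedence or limits the mother's report to children whose card is not seen.

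On blinding, Study Design says "Enumerators will be blind to the assignment of the intervention". Nothing is said of mothers, and they could not be blind. The script given at home in two arms covers, among other things, "the individual benefit of the combination vaccine in terms of mortality and morbidity gains". For the remaining arm, "The third arm acts as a control group with no information given to the mother".

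The Analysis section and the appendix on deviations describe no card-confirmed version of the primary comparison. The survey section lists the presence of a card among the baseline items and says that the endline tool will be very similar. Table 2 has a row "Children 12-23 months with immunization card", which gives card possession in the general population of each study district.

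**The concern.** The intervention tells a mother that vaccinating her child is the right thing to do. Nine months later the same study asks her whether she did it, and her answer can decide the primary outcome. Control mothers have had no such message. If some informed mothers say yes when the child has not had three doses, the error falls mostly in the information arms and has the sign of the hypothesis.

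The stated question is whether information changes uptake. With card and report merged, a positive result could be uptake, reporting or a mixture, and the planned analysis could not tell them apart. The protocol itself fixes this definition, so it is more than a detail left to a statistical analysis plan.

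**Working it through.** **1. The plan's benchmark.** Sample Size Calculations gives a detectable difference of about 7 points for the pooled comparison when 10% of controls have three doses. Table 3 shows 288 control and 576 pooled children. With p1 = 0.10, p2 = 0.17, allocation ratio k = 2, two-sided 5% and 80% power:

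- pooled proportion = (0.10 + 2 × 0.17)/3 = 0.1467
- n(control) = [1.960 × √(1.5 × 0.1467 × 0.8533) + 0.842 × √(0.10 × 0.90 + 0.17 × 0.83/2)]² / 0.07²
- = (0.8492 + 0.3372)² / 0.0049 = 287.3, rounded up to 288.

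The figure reproduces, so 7 points is a sound yardstick.

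**2. Bias model.** With no true effect, bias = s × (1 − p) × e, where

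- s = share of children classified on the mother's report alone;
- p = proportion truly vaccinated, 10% as in Table 3 (only the other 90% can be falsely reported);
- e = excess probability of a false report in the information arms over control.

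The protocol gives neither e nor card possession among enrolled children. I assume e = 10 to 20 points.

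**3. No-card share from Table 2** (100 minus card possession): Kannauj 34.0, Kanpur Nagar 7.6, Kanpur Dehat 8.0, Auraiya 19.7, Etawah 7.9, Fatehpur 11.8.

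- Unweighted mean: 89.0/6 = 14.8%.
- Weighted by the Table 1 populations: 178.06/13.7 = 13.0%.

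**4. Bias.**

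| Assumption about s | s | e = 10 points | e = 20 points | e needed for 7 points |
|---|---|---|---|---|
| Six districts, population-weighted | 13.0% | 1.2 | 2.3 | 60 |
| Six districts, unweighted | 14.8% | 1.3 | 2.7 | 52 |
| Lowest-possession district (Kannauj) | 34.0% | 3.1 | 6.1 | 23 |
| Report accepted for every child (literal *or*) | 100% | 9.0 | 18.0 | 7.8 |

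The first three rows assume that report is used only where there is no card.

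Table 2 describes all children aged 12 to 23 months, whereas every enrolled child lacks the third dose. As an upper bound, suppose that all card-less children are among those without it. Then s = no-card share / (1 − DPT3 coverage). This runs from 7.9/30.8 = 26% (Etawah) to 34.0/40.9 = 83% (Kannauj). The bias is then 2.3 to 7.5 points at e = 10, and 4.6 to 15.0 at e = 20.

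**5. Consequence for the test.** Approximate two-sided rejection probability at 288/576 with 10% in controls and no true effect:

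| Bias (points) | 0 | 1 | 2 | 3 | 5 | 7 |
|---|---|---|---|---|---|---|
| False-positive rate | 5% | 7% | 13% | 24% | 53% | 80% |

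**The case against.** Several counter-arguments have force.

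- **Size.** A reader might infer that over-reporting alone could plausibly produce the whole 7-point difference. The documents do not support that as a central expectation. With report used only as a fallback, even 6.1 points needs the worst district's card possession throughout and a 20-point excess that no passage supports. At the six-district average, 7 points would need an excess above 50. This stands, and the central range is therefore 1.2 to 2.7 points.
- **Cues in every arm.** All mothers are told the purpose of the study and asked about vaccination and tetanus at baseline, and the endline comes nine months later. Only the excess in the information arms matters, and it may be small. This stands as a reason for caution about e. It does not make e zero.
- **Screening.** Eligibility also rests on card or self-report: staff "assess eligibility based on either vaccination cards or self-reports, and seek informed consent". A reader might infer that doses given before baseline but discovered later bias the result towards the hypothesis. That does not follow: the misclassification precedes the information and should be balanced between arms by randomisation.
- **Statistical analysis plan.** A supporting card-only analysis is often placed there, and its absence alone would not be a finding. The outcome definition, however, is in the protocol and is silent on precedence.

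**Conclusion.** The point holds as a weakness in the definition of the primary outcome. The reporter is unblinded, only the information arms are taught the desired answer, and her word counts equally with the card. The direction of any resulting bias favours the intervention.

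The size is conditional. On an assumed excess of 10 to 20 points among unvaccinated children without a card, and the districts' average card possession, it is about 1.2 to 2.7 points. It rises to about 6 at the lowest district's possession, and further if card-less children are concentrated among the under-vaccinated or if *or* is applied literally to children with a card. Even 2 to 3 points would raise the false-positive rate to about 13 to 24%, so the bias need not approach 7 points to matter. None of this shows that over-reporting will occur. It shows that the primary result as defined could not rule it out.

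**What to change.** 1. State in the outcome definition that the card decides whenever it is seen, and that the mother's report is used only when it is not. This removes the bias for children with a card, which is the literal *or* case. It does not touch the card-less component.
2. To address that component, add a card-confirmed sensitivity analysis of the pooled comparison, counting a child without a card at endline as not confirmed. Report the proportion card-verified in each arm beside it.
3. If the card-confirmed and composite results diverge in direction, describe the effect as reported rather than verified uptake.

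The cost is wording and one analysis on data that the surveys appear to collect. The appendix on deviations indicates that outcome analyses have already been completed. An analysis added now should therefore be labelled as such.

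The downside is a smaller absolute difference. If 13 to 34% of children lack a card equally in all arms, a true difference of 10% against 17% becomes 7 × 0.87 = 6.1 to 7 × 0.66 = 4.6 points. Power at 288/576 falls from 80% to about 73 to 59%. Informed mothers may also keep or find cards more often, which would bias the card-confirmed result itself. It should therefore support the primary analysis, and the claim of an effect should not depend on the two estimates being of similar size.

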## Sample Size Calculations

Table 3 shows the detectable difference between a single treatment group and the control group for a range of sample sizes and assumed proportions of children in the control group with three doses of DPT vaccination one year after baseline. These calculations are based on 80 percent power and 5 percent level of significance. Assuming 10 percent of children in the control group with three doses of DPT vaccination one year after baseline, the study will be able to detect a difference between a single treatment group and the control group of 8 to 9 percentage points. If the assumed proportion of children in the control group with three doses of DPT vaccination is 20 percent, then the detectable difference is slightly more than 10 percentage points. Note that the inclusion of baseline covariates should improve the precision of estimates. The second part of Table 3 shows sample size calculations when the comparison is between the two treatment groups pooled together and the control group. In this comparison, the minimum detectable difference given the sample size available to the study is approximately 7 percentage points under the assumption that 10 percent of children in the control group have three doses of DPT vaccination one year after baseline.

Table 3. Sample size calculations

|  | Effect size (percentage point difference between groups) | | | | | |
| --- | --- | --- | --- | --- | --- | --- |
|  | 5 % | 6 % | 7 % | 8 % | 9 % | 10 % |
| **1. Comparison between single intervention group and control group** | | | | | | |
| P_1_ is 10 percent | 686 | 492 | 373 | 295 | 240 | 199 |
| P_2_ is 20 percent | 1094 | 772 | 575 | 447 | 358 | 294 |
|  |  |  |  |  |  |  |
| **2. Comparison between two treatment groups pooled and control group** | | | | | | |
| P_1_ is 10 percent | 526/1052 | 379/758 | 288/576 | 228/456 | 185/370 | 155/310 |
| P_2_ is 20 percent | 829/1658 | 585/1755 | 437/874 | 340/680 | 273/546 | 224/448 |

Notes: Sample size calculations based on individual randomization, 80 percent power and 5 percent level of significance. The second part of the table examines sample sizes for a comparison of the two treatment groups and the control group showing the sample size in the control group / two treatment groups pooled. The cells highlighted indicate the approximate sample size available to the study.

## Data Collection

A number of data collection activities are envisaged as part of the overarching study evaluating the social franchise project. These data collection tools have been designed to accommodate the research objectives contained within this study protocol. In others words, this study will piggyback on the data collection activities of the overarching evaluation.

### Identification of participants

Potentially eligible participants were identified through two channels. First, a household survey conducted by the research team for a different purpose nine months prior to the study will be useful in identifying eligible women to participate. The household survey will use the sampling frame provided by the most recent census, conducted in 2011. The sampling is based on a two-stage design. The first stage involves the selection of 180 primary sampling units or clusters using systematic sampling proportional to size. The second stage involves a full household listing on entry to the cluster to create the sampling frame of eligible women (i.e. gave birth in previous two years). From this sampling frame 20 eligible women per cluster will be selected at random and invited for interview. Second, a list of mothers who have given birth in the past year provided by the community health worker (known as ASHAs) in each village will also identify eligible women to participate. Study researchers will visit the household of each potentially eligible mother, assess eligibility based on either vaccination cards or self-reports, and seek informed consent.

### Initial and final household survey

A baseline survey of eligible women will capture information on: 1) the presence of a vaccination card; 2) whether the child has been vaccinated against tuberculosis, diphtheria, pertussis, tetanus, polio and measles, respectively; 3) the mother’s knowledge of tetanus symptoms, and 4) the mother’s perceptions of the efficacy of tetanus vaccination. The latter will be measured using an established technique in which women are asked to ascertain the likelihood of various events happening by placing beans in a cup. The endline survey will use a very similar tool nine months after the baseline survey.

## Analysis

The primary analysis will compare the proportion of children with three doses of DPT in the two treatment groups pooled together against the control group. A logistic regression with a dummy variable representing the two treatment groups combined will produce risk ratios with 95% confidence intervals adjusted for the distance stratifying variable (included as two dummy variables), with the control group as the omitted reference category. Fully adjusted risk ratios will also be generated with the inclusion of baseline characteristics. Secondary outcomes will be analysed in a similar manner, but using OLS in the case of continuous outcomes.

Several additional analyses will be conducted. First, an analysis to identify the effects of the two variants of the intervention will be conducted in a treatment group analysis. Each of the three groups will be compared against each other. The comparison between the two information groups will identify whether framing matters. Second, an analysis of information spillovers will be conducted by exploiting random variation in the geographical density of households assigned the treatment groups ([Dupas, 2014](#_ENREF_5), [Kremer and Miguel, 2007](#_ENREF_12), [Miguel and Kremer, 2004](#_ENREF_19)). Information on the geographical coordinates of households will be used to generate a variable that indicates for each household the share of other households within a given radius who received the information intervention. The presence of information spillovers is examined by the inclusion of this density variable. The sensitivity of the results to different radii will be explored (ie. 250 metres, 500 metres, 750 metres). Third, differences in the primary endpoint across specified subgroups will be assessed by adding a treatment-by-subgroup interaction terms to the binary regression models. This will be done separately for the following subgroups measured at baseline: 1) index of the mother’s perception of the efficacy of tetanus vaccination; 2) gender of the child; 3) household wealth; 4) education level of the mother; and 5) distance to the nearest government facility. In the analysis of secondary outcomes, OLS will be used in the case of continuous outcomes.

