## Deviations from the study protocol

There were deviations from the study protocol as follows:

- Before the baseline household survey and the delivery of the information intervention, the secondary outcome measuring the proportion of children fully vaccinated was re-defined to no longer include polio, as originally stated in the study protocol. We did not collect any information on polio vaccinations in the household surveys.
- Prior to the data analysis, we planned to analyse the following additional secondary outcomes: the proportion of children with measles vaccination, the proportion of children with BCG, the mother’s knowledge of any cause of tetanus and her knowledge of any prevention method.
- In the study protocol, it stated that we would conduct subgroup analyses with respect to: 1) index of the mother’s perception of the efficacy of tetanus vaccination; 2) gender of the child; 3) household wealth; 4) education level of the mother; and 5) distance to the nearest government facility. The last three subgroup analyses were not conducted because we did not collect data on household wealth, education or distance to the nearest government health facility.
- The original protocol stated that a logistic regression would be used to produce odd ratios of the effect of the information intervention. Since simple randomisation was used that involved no stratification, we resorted to basic statistics to show the absolute difference and the relative risk between groups, with their corresponding 95% confidence intervals.
- We conducted several analyses that were unplanned. We decided to do these analyses after we had completed the analysis of the pre-specified outcomes, hence they are exploratory. First, we compared the mean in our measure of perception of DPT vaccine efficacy between treatment and control for two subgroups of women, with baseline perception of efficacy above and below the 50% threshold, respectively. Second, we carried out a cost-effectiveness analysis.

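### The first-stated OLS model for the tetanus-knowledge and perceived-efficacy indices does not use their baseline values, so precision already paid for may be lost

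*Protocol*

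**What the plan says.** The Outcomes section lists among the secondary outcomes "an index of the mother’s knowledge of tetanus symptoms, and 3) an index of the mother’s perception of the efficacy of tetanus vaccination". Under Initial and final household survey, the baseline questionnaire also covers "the mother’s knowledge of tetanus symptoms, and 4) the mother’s perceptions of the efficacy of tetanus vaccination", and "The endline survey will use a very similar tool nine months after the baseline survey". Each index is therefore planned to be measured twice on every mother.

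The Analysis section defines the first model for the primary outcome as a regression on a pooled-treatment indicator, "adjusted for the distance stratifying variable (included as two dummy variables), with the control group as the omitted reference category". A second model follows: "Fully adjusted risk ratios will also be generated with the inclusion of baseline characteristics". The continuous secondary outcomes take over this structure: "Secondary outcomes will be analysed in a similar manner, but using OLS in the case of continuous outcomes". No sentence names the baseline value of either index as a covariate when that index is the outcome.

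The Appendix (Updates to the original study protocol) states that randomisation was simple, 1:1:1 and unstratified, and that distance to the nearest public facility was not collected. Under Sample Size Calculations, the protocol itself remarks that baseline covariates should make the estimates more precise.

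**The concern.** With the distance term unavailable, the first-stated model contains the treatment indicator and nothing else. For each index it gives the difference in nine-month means. Differences between mothers that were already present at baseline, and were measured, stay in the residual variance. Because allocation was simple, nothing in the design balances baseline knowledge or perception across arms, and part of any chance difference carries into the unadjusted estimate.

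The Study Objectives section supposes that information shifts perceptions and so raises demand and uptake. The perception index is the pre-specified measure of that step. An imprecise estimate makes a real but modest shift easier to miss. The same applies to the comparison of gain and loss framing, which rests on fewer mothers than the pooled comparison.

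**Working it through.** **Inputs.** Two-sided 5% level and 80% power (Sample Size Calculations; two-sided is the reading that reproduces Table 3). Pooled treatment against control is 2:1, from the 1:1:1 allocation. The protocol gives no SD, power or correlation for either index, so effects are in SD units and rho is assumed over 0.1 to 0.7. No loss to follow-up is assumed.

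**Sample size, reproducing Table 3.** The text gives a detectable pooled difference of about 7 points at a 10% control proportion. With p1 = 0.10, p2 = 0.17 and k = 2:

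- p̄ = (0.10 + 2 × 0.17)/3 = 0.1467
- n(control) = [1.96 × √(1.5 × 0.1467 × 0.8533) + 0.8416 × √(0.09 + 0.1411/2)]² / 0.07² = (0.849 + 0.337)²/0.0049 ≈ 287.3, rounded up to 288

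This matches the 288/576 cell. The same formula reproduces all 24 single-arm and control-arm figures in Table 3. The single-arm statement (8 to 9 points at 10%) corresponds to 295 to 240 per arm, so 288 lies within the range.

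**Unadjusted comparison of an index.** SE = √(1/288 + 1/576) = 0.0722 SD. Detectable difference = (1.96 + 0.84) × 0.0722 = 0.202 SD.

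**Adjusted for the baseline index.** SE(adj) = 0.0722 × √(1 − rho²). Power for a true effect of 0.202 SD = Φ(0.202/SE(adj) − 1.96). Equivalent control-arm size = 288/(1 − rho²). Carry-over of a chance baseline difference of 1.96 SE into the unadjusted estimate = rho × 1.96 × 0.0722.

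| rho | Variance ratio | Detectable difference (SD) | Power | Equivalent control n | Carry-over (SD) |
|---|---|---|---|---|---|
| 0 | 1.00 | 0.202 | 80.0% | 288 | 0 |
| 0.1 | 0.99 | 0.201 | 80.4% | 291 | 0.014 |
| 0.3 | 0.91 | 0.193 | 83.6% | 316 | 0.042 |
| 0.5 | 0.75 | 0.175 | 89.9% | 384 | 0.071 |
| 0.7 | 0.51 | 0.144 | 97.5% | 565 | 0.099 |

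The gain reaches 5 points of power at rho of about 0.36. At 240/480 the power column and the variance ratios are unchanged, and the unadjusted detectable difference is 0.221 SD.

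**Framing comparison, 288 against 288.** SE = √(2/288) = 0.0833 SD. Detectable difference = 2.80 × 0.0833 = 0.233 SD unadjusted, and 0.233 × √0.75 = 0.202 SD at rho 0.5.

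**The case against.** The strongest reply is that adjustment is already planned. The instruction to treat secondary outcomes similarly carries over the fully adjusted model as well as the first one, and nothing bars the baseline index from it. Naming covariates for secondary outcomes is often left to a statistical analysis plan. This stands in part: it would be wrong to say that the protocol rules out baseline adjustment. But the protocol does fix the covariate of its first model, that covariate was not collected, and nothing ensures that the baseline index enters the second.

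A second reply is that this is a matter of efficiency and not an error. That stands. Under randomisation the unadjusted contrast is unbiased on average and its confidence interval already allows for chance imbalance. Only about rho times a baseline difference carries over, not all of it.

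A third reply is that the benefit rests wholly on an assumed correlation. That also stands. Nothing in the protocol supports a particular rho over nine months, and at 0.3 or below the gain is under 4 points of power.

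A reader might infer more than the text supports:

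- The two surveys are described as using a very similar tool, not an identical one. Adjustment does not need identical tools.
- The baseline data "used to examine the balance of the treatment and control groups" are characteristics of the study population. That sentence does not mention the indices.
- The indices are not the only evidence on mechanism. The Appendix adds knowledge of any cause and of any prevention method of tetanus, and the planned interaction of treatment with baseline perception on the primary endpoint also bears on it.
- The Appendix reports that "we compared the mean in our measure of perception of DPT vaccine efficacy between treatment and control for two subgroups of women". This is a completed analysis labelled exploratory, and defining groups by baseline perception was its purpose. It does not support the present point.

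**Conclusion.** The point holds as a modest, nearly free improvement to the analysis of two secondary outcomes. The first-stated model reduces to an unadjusted nine-month difference although the baseline value of each index is collected, and the only route to adjustment is a supporting model with unnamed covariates. The cost is lost precision and weaker protection against chance imbalance. It ranges from negligible (0.4 points of power at rho 0.1) through 3.6 points at 0.3 and 9.9 at 0.5 to 17.5 at 0.7. This rests on the 288/576 size read from Table 3, full follow-up and the assumed rho.

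It would go too far to conclude that the planned comparison is biased or invalid, or that the trial's main result is at risk. DPT3 is a separate outcome: children who already have three doses are excluded at entry, so it has no baseline variation to adjust for.

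**What to change.** In the Analysis section, remove the distance term for these outcomes and replace the general sentence on continuous secondary outcomes with wording such as: *The knowledge and perception indices will each be analysed by OLS of the nine-month value on treatment, adjusting for the same index at baseline as a continuous covariate. This is the lead estimate; the unadjusted difference in means is supportive.* Use the same model for the three-group comparisons, including the framing contrast.

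The cost is a sentence or two of wording and one covariate that the baseline survey already plans to collect, with no new data or participants. If rho proves near zero, the loss is one degree of freedom. The Appendix describes analyses as already carried out. If the indices have been analysed, report the adjusted estimate beside the unadjusted one and state when it was added.
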